#### 11.4.2 Primary Analysis

We will test intervention effects over time by comparing groups on the 2 primary and 6 secondary outcomes. For repeated measures, analyses will be conducted using generalized estimating equations (GEE) with robust standard error estimate (Liang and Zeger, 1986). This approach offers an extension of regression analysis to the case of correlated observations over time; it allows for specification of the assumed correlation structure as well as the appropriate link functions to handle dependent variables with a normal distribution, dichotomous outcomes, count data (Poisson), and over-dispersed count data (negative binomial). Models will all be adjusted for the baseline AUDIT score. For outcomes measured at 12-month only, analyses will be conducted using baseline adjusted regression models.

Analyses will be performed at the completion of data collection.

Analyses will be performed by the study PI ([name]), in collaboration with research collaborator [name], and consulting from study co-Is ([name], [name], [name]) and international collaborators ([name], [name]).

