### 7.2 Recruitment and screening

The study will be conducted at the Lausanne University Hospital ER, Switzerland. According to administrative data over 7 weeks randomly selected between November 2012 and March 2013, intoxicated young adults are admitted almost only in the later part of the week. For economic reasons, we will limit study recruitment in the ER to Thursday to Sunday mornings from 7am to 2pm, covering 85% of eligible patients. Patients meeting inclusion criterion and having been treated outside this time frame will be contacted by phone and proposed to come to Lausanne University Hospital Alcohol Treatment Center to participate in the study.

All consecutive patients between the age of 18 and 35, admitted in the ER (for any cause) and having alcohol intoxication (>0.5 gram/liter BAC or clinical indication of alcohol intoxication) will be contacted by a member of the research staff during study period. Patients meeting inclusion criterion but being too intoxicated will be contacted by research staff once they have sobered up.

First, research staff will conduct a screening process to evaluate inclusion and exclusion criterion (see Chapter 7.1 above). In case only exclusion criteria e) is not fulfilled (i.e. psychiatric or medical contra-indications preventing patients understanding informed consent, fulfilling questionnaires, and participating in the intervention; evaluated using an adaptation of the University of California, San Diego Brief Assessment of Capacity to Consent – UBACC; McCormack et al. 2014), research staff will come back later to re-assess UBACC and complete further study process if the UBACC score is positive.

For those included, baseline assessment questionnaire will then be conducted in the ER, in a separate space providing confidentiality and using a tablet-based electronic questionnaire administered by a research clinician. The questionnaire will be short (about 5 minutes), first as patients might be hung-over as a result of alcohol intoxication, and second to reduce reactivity to alcohol assessment which has been shown as a source of bias (Gallen, 1974; McCambridge & Kypri, 2011).

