| Expected duration (minutes)                                                                                                                                                                                                                      | 15                 | BMI: 20-60
BA: 5-10 | 5                 | 15-20     | 20-30 | 20-30                           | 5 | 15-20                      | 5 |
| In- /Exclusion Criteria                                                                                                                                                                                                                          | x                  |                        |                   |           |       |                                 |   |                            |   |
| Patient Information and Informed Consent                                                                                                                                                                                                         | x                  |                        |                   |           |       |                                 |   |                            |   |
| Demographics (questionnaire)                                                                                                                                                                                                                     | x                  |                        |                   |           |       |                                 |   |                            |   |
| Primary outcomes variables (questionnaires)                                                                                                                                                                                                      | x                  |                        |                   | x         | x     | x                               |   | x                          |   |
| Secondary outcomes variables (questionnaires)                                                                                                                                                                                                    | x                  |                        |                   | x         | x     | x                               |   | x                          |   |

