## **9.3 Procedures at each visit**

### **9.3.1 Day 1 – Inclusion, Baseline procedures, Intervention (in the ER)**

- A. Inclusion/Exclusion criteria from medical file/ER exam
  - Age
  - Blood alcohol concentration at admission (test made by ER staff)
  - Life threatening conditions
  - Detainees or medico-legal admissions
  - Medical or psychiatric contraindications preventing contact with patient
- B. Inclusion/Exclusion criteria assessed by research staff
  - Being fluent in French
  - Not currently receiving another alcohol or substance use treatment
- C. Consent process
  - Information sheet
  - No psychiatric or medical contra-indications preventing patients understanding informed consent, fulfilling questionnaires, and participating in the intervention (evaluated using an adaptation of the University of California, San Diego Brief Assessment of Capacity to Consent; McCormack et al. 2014)
  - Signing consent form
- D. Contact information
  - Name, Address, Phone
- E. Baseline questionnaire
  - Socio-demographic questions
  - Alcohol Use Disorder Identification Test
  - Substance use
  - Attribution of ER admission to alcohol
  - Readiness Rulers
  - Alcohol-related expectancies
  - Actual-ideal drinking discrepancy
  - Depression
  - Quality of Life
- F. Randomization
  - Software-based automatic allocation to study group (BMI vs BA)
- G. Intervention
- H. Post-session questionnaire
  - Patient rating of the treatment (paper/pencil questionnaire to be placed in a sealed envelope by the participant and later entered by research assistant to avoid that research

- clinicians have access to participant's rating of the session)
  - Readiness Rulers
  - Actual-ideal drinking discrepancy
- I. Counselor's rating of the treatment
  - Working alliance inventory
- J. Head hair sampling for Ethyl Glucuronide concentration analysis
  - Additional information and consent procedure
  - Sampling of 2-3 centimeters long strand of hair (diameter of pencil lead)
- K. Additional information on admission (medical records, not in presence of patient)
  - Admission and discharge time
  - Diagnosis
  - Use of restraints
  - Passage in resuscitation area
  - Orientation at ER discharge

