### **9.3.3 Month 3, by phone**

- Alcohol use (30-day timeline follow-back)
- Alcohol problems and consequences
- Readiness to change questionnaire
- Alcohol Abstinence Self-efficacy Scale – Reduced drinking
- Alcohol-related expectancies
- Actual-ideal drinking discrepancy
- Substance use
- Quality of life
- ER readmission
- Alcohol treatment

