## **11. STATISTICAL METHODS**

### **11.1 Hypothesis**

The primary aim of the randomized controlled trial is to test the efficacy of the brief motivational intervention model developed in the first part of this project by comparing it to a control condition receiving a minimal intervention (structured brief advice).

The Null hypothesis is that both interventions have comparable effects in reducing

- a) the number of Heavy drinking days (HDD, i.e. the number of days with 6 standard drinks or more, equivalent to 60 grams of pure alcohol or more, over the last month), and
- b) alcohol-related problems as measured by the Short Inventory of Problems (SIP) total score, over 3 the follow-up times (3-, 6-, and 12-month after intervention).

The Alternative hypothesis is that participants in the Brief motivational intervention group (experimental condition – intervention model developed in the first phase of the project) reduce

- a) the number of Heavy drinking days (HDD, i.e. the number of days with 6 standard drinks or more, equivalent to 60 grams of pure alcohol or more, over the last month), and
- b) alcohol-related problems as measured by the Short Inventory of Problems (SIP) total score, more than participants in the control group (structured brief advice) over the 3 follow-up times (3-, 6-, and 12-month after intervention).

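### Table 9.1 marks the primary outcomes at baseline, the Day 1 list in 9.3.1 omits both, and the models name only AUDIT as covariate: the passages need reconciling, for precision rather than validity

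*Protocol*

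**What the plan says.** - **Protocol 9.1, table of procedures.** The row "Primary outcomes variables (questionnaires") carries a mark at baseline (time 0) and at months 1, 3, 6 and 12.
- **Protocol 9.3.1, Day 1.** Under "E. Baseline questionnaire" the only alcohol-severity instrument is the "Alcohol Use Disorder Identification Test". The other items are socio-demographics, substance use, attribution of the admission to alcohol, readiness, expectancies, drinking discrepancy, depression and quality of life. There is no timeline follow-back and no SIP.
- **Protocol 9.3.2 to 9.3.6, follow-up calls.** The timeline follow-back has its own line, "Alcohol use (30-day timeline follow-back"), at months 1, 3, 6 and 12. Problems have theirs, "Alcohol problems and consequences", at months 3, 6 and 12.
- **Protocol 5.1, 9.2.1 and 11.1.** Both primary outcomes are defined at 3, 6 and 12 months.
- **Protocol 11.1.** The null hypothesis is that "both interventions have comparable effects in reducing" HDD and SIP. The alternative is a larger reduction in the motivational arm than in the control arm.
- **Protocol 11.4.2.** "Models will all be adjusted for the baseline AUDIT score". The baseline-adjusted regressions mentioned there apply to outcomes measured only at 12 months, so not to HDD or SIP.

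**The concern.** The table and the visit list cannot both be right about what is asked on Day 1. Staff working from the table would administer two instruments that staff working from the list would not.

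Each reading leaves something to settle in the analysis. If the table is right, each primary outcome has a baseline of its own, and the named model does not use it. AUDIT is then a stand-in with a 12-month reference period, whereas HDD covers 30 days. If the visit list is right, there is no pre-intervention HDD or SIP. Reduction within an arm then cannot be reported, although section 11.1 is worded in terms of reduction.

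The stake is modest: the precision of the two primary comparisons, and a hypothesis that matches the data collected.

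**Working it through.** **1. Which passage is likelier to be wrong?**

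- Section 7.2 limits the baseline on purpose: "The questionnaire will be short (about 5 minutes), first as patients might be hung-over as a result of alcohol intoxication". Its second reason is to reduce reactivity to alcohol assessment. Leaving out a day-by-day drinking calendar and a 15-item problem scale fits that aim.
- Sections 5.1, 9.2.1 and 11.1 give the outcome times as 3, 6 and 12 months. The Synopsis counts four follow-ups, but it does not list a baseline either.
- The table row is coarse. It marks the primary outcomes at month 1, where the list in 9.3.2 has the timeline follow-back but no problem measure.
- The follow-up lists name both measures wherever they are collected, so their absence from Day 1 is unlikely to be loose listing.

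These points make the table the likelier error, but they do not prove it.

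**2. The plan's own sample size.** Section 11.2 gives 172 per group for effect size .25, power .8 and alpha .05 (taken as two-sided), with attrition of 5-20%. It mentions no covariate and gives no value for the correlation.

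- One time point: 2 × (1.96 + .84)² / .25² ≈ 251.2, so 252 per group.
- Mean of three visits at an assumed constant correlation ρ = .5: variance factor (1 + 2 × .5)/3 = .667. Then 251.2 × .667 ≈ 167.4, so 168 per group without attrition.
- With retention of 95, 87.5 and 80% over three visits and ρ = .5: 183 per group if the correlation is constant over time, 176 with moderate damping and 172 with stronger damping.

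The stated 172 is thus compatible with a correlation near .5. It cannot be reproduced exactly, because the correlation is not stated.

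**3. What a covariate could add.** Take .80 as the unadjusted power, three visits, ρ = .5 and no attrition. Let the covariate correlate r with each follow-up. The variance factor falls from .667 to .667 − r², and

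power = Φ(2.80 × √(.667 / (.667 − r²)) − 1.96).

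| r | .667 − r² | Power |
|---|---|---|
| 0 | .667 | .80 |
| .2 | .627 | .82 |
| .3 | .577 | .85 |
| .4 | .507 | .89 |
| .5 | .417 | .94 |
| .6 | .307 | .98 |

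If AUDIT has r = .3 and baseline HDD r = .5, the step is from about .85 to about .94. The variance ratio is .417/.577 = .72, a cut of 28%. Each row treats one covariate alone.

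**4. Cross-check with attrition.** With 172 per group, the retention above, ρ = .5 and moderate damping, power is .79 with no covariate, .82 to .85 for a proxy at r = .2 to .3, and .89 to .99 for an own baseline at r = .4 to .6. The picture is the same.

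Every r and ρ here is an assumption; the protocol gives none.

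**The case against.** The strongest reply is that the documents largely settle the question. The questionnaire is short by design, AUDIT is the natural covariate when it is the only alcohol-severity measure taken on Day 1, and the time-0 mark is a slip in a coarse table. On that reading no data are discarded. Most of this stands, and it limits the point to a reconciliation with a modest consequence.

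A reader might go further than the text allows in four ways:

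- **That the trial cannot test its hypothesis.** Under randomisation the arms have the same expected baseline. The difference between arms at follow-up therefore estimates, on a linear scale, the difference in reduction. Section 11.1 sets a comparison with control, and 11.4.2 tests it by comparing groups. Only within-arm reduction is lost. No bias or invalid test follows.
- **That other covariates are excluded.** Section 11.4.2 names the AUDIT score and bars nothing else. Further covariates may stand in an analysis plan that is not at hand.
- **That the planned .80 already includes AUDIT.** Section 11.2 mentions no covariate, so .80 is better read as unadjusted power. That is why the comparison above starts at .85.
- **That the secondary-outcome mark at time 0 is equally wrong.** AUDIT is a secondary outcome measure and is on the Day 1 list, so that mark is at least partly right.

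What the reply does not remove is the contradiction about what is collected on Day 1. It also does not explain why, if the baselines do exist, the named model should leave them out.

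**Conclusion.** The point holds as an inconsistency between Table 9.1 and section 9.3.1, with a consequence for the covariates in 11.4.2 and the wording of 11.1. The table is the likelier error. The AUDIT-adjusted comparison between arms is valid whichever passage is right.

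The size depends on which passage is right:

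- **If baseline HDD is collected**, using it could raise power from about .85 to about .94 (AUDIT r = .3, baseline HDD r = .5, three visits, ρ = .5, no attrition, .80 unadjusted). There is no gain if the two correlate equally with follow-up and baseline HDD adds nothing beyond AUDIT. The SIP was not worked separately.
- **If it is not collected**, those figures do not apply. The gain from other baseline items is not quantified and is probably small.

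Confidence is high for the inconsistency and low for any particular power figure. The change is worth making because it costs little.

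**What to change.** 1. Reconcile Table 9.1 with section 9.3.1 so that both state the same Day 1 instruments.
2. If baseline HDD and SIP are collected, list both in 9.3.1. In 11.4.2, add baseline HDD to the HDD model and baseline SIP to the SIP model, each alongside AUDIT.
3. If they are not collected, delete the time-0 mark for the primary outcomes. Word 11.1 as fewer HDD and lower SIP over 3, 6 and 12 months than in the control arm, and claim no within-arm reduction. If AUDIT item scores are stored, which the protocol does not say, add the heavy-drinking-frequency item to the HDD model. Age and sex are optional, since nothing in the protocol shows that they predict either outcome.
4. Correct the month-1 mark in the same row, since the month 1 list has no SIP.

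The cost is a few lines of protocol text and one or two covariates already held, with no added burden on participants. Section 2.3 counts changes to endpoints or to the form of the analysis among significant changes, so ethics committee approval may be needed.

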#### 11.4.3 Secondary Analyses

Analyses of intervention mechanisms (Aim 3 of the project) will include the following analyses:

*Moderation.* Separate GEE models will test the main effect of treatment on outcome, followed by the effect of each moderator variable, and then the interaction of the treatment with each moderator variable.

*Mediation.* To examine mediators of the main effect of the MI intervention on outcomes, we will use Model 4 of the PROCESS algorithm developed by Hayes (2013). Here, regression analyses are used to test path *a* (the effect of the treatment condition on the hypothesized mediators) and path *b* (the effect of each respective mediator on outcomes, while also controlling for the treatment effect on outcomes). Then indirect effects are estimated using bootstrapping, a nonparametric resampling procedure that does not impose the assumption of normality of the sampling distribution (Hayes, 2013; Preacher & Hayes, 2008).

*Moderated mediation* aims at measuring if the effect is transmitted through the designated mediators only under specific circumstances. Several models of the PROCESS algorithm (e.g. 7, 9, 58) allow calculation of moderated mediation (also known as conditional indirect effects) (Hayes, 2013) (Hayes, 2013). These different models specify which path (*a*, *b*, both) of the mediated relationship are moderated. As in mediation, bootstrapping is used to derive conditional indirect effects.

*Qualitative analyses.* In addition to the quantitative analysis of interventions' mechanisms exposed above, we will use qualitative techniques to analyze intervention and follow-ups feedback. A random sub-sample of 20 BA and 20 MI sessions will be transcribed and analyzed using thematic analysis and recursive abstraction techniques (Maxwell, 2005). In addition, semi-structured interviews will be conducted after the 1-month and 12-month follow-up questionnaire with another randomly selected 10 patients having received BA and 10 MI sessions. Topics addressed will be qualitative assessment of potential short-/long-term changes experienced during the follow-up period and their relation or not with the intervention received.

Regarding hypotheses, the proposed research will be one of the first prospective study designed to evaluate the mechanisms of alcohol BMI outcomes, which is in line with recently recommended priorities in clinical trial design (Longabaugh and Magill, 2011). Specifically, we will analyze treatment effects within a larger conceptual framework of mechanisms of behavior change (see Figure below). The mechanisms investigated here are all indicated as promising candidate variables in the seminal monograph on factors impacting addiction treatment effects recently published by Miller and Moyers (2015). In this model, the main effect (red arrow) between treatment and change in alcohol use (distal outcome) is explained (or mediated) by therapists' and patients' within-session behaviors (e.g. MI skills and change language), by the patients' experience of the treatment, and by patient proximal cognitive or behavioral changes (e.g. increased self-efficacy, readiness to change, Longabaugh *et al.*, 2005; Moos, 2007). Patient behaviors during treatment might influence their experience of the treatment and thus their outcome, but also influence therapist behaviors (as indicated by bidirectional arrow; e.g. Moyers and Martin, 2006; Gaume *et al.*, 2010). Finally, what happens during the session (therapist and patient behaviors) may be influenced by several moderating factors (e.g. Karno and Longabaugh, 2007; Gaume *et al.*, 2009; Gaume *et al.*, 2016).

These factors mainly are the therapist and patient characteristics, such as age, gender, therapist clinical experience, patient alcohol problems severity, readiness to change, or personality. (Note: our design will not permit tests of therapist characteristics which will be underpowered).

[figure not shown]

Quantitative analyses will be performed by the study PI ([name]), in collaboration with research collaborator [name], and consulting from study co-Is ([name], [name], [name]) and international collaborators ([name], [name]).

Qualitative Analyses will be performed by research collaborator [name] and [name], with consulting from study PI ([name]), co-Is ([name], [name], [name]), and international collaborators ([name], [name]).

Analyses will be performed at the completion of respective data collection, but at least after the completion of all interventions (e.g. qualitative analysis of participants' experience at 1-month follow-up will not be performed before completion of all interventions in order not to influence intervention content).

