### 5.3 Other Outcomes of Interest

Additional measures for intervention mechanisms study will also be assessed at different time points (see table below) in order to conduct moderation and mediation analysis (see chapter 11.4.3 Secondary analysis).

|                                                                    | Baseline | Post-session | 1-month | 3-month | 6-month | 12-month |
|--------------------------------------------------------------------|----------|--------------|---------|---------|---------|----------|
| Alcohol use disorder severity (Babor et al. , 2001)         | x        |              |         |         |         |          |
| Readiness Rulers (Rollnick, 1998)                                  | x        | x            |         |         |         |          |
| Actual-ideal discrepancy (McNally et al. , 2005)            | x        | x            | x       | x       | x       |          |
| Alcohol-related expectancies (Ham et al. , 2005)            | x        |              | x       | x       | x       |          |
| Depression/Anxiety (Kroenke et al. , 2009)                  | x        |              |         |         |         |          |
| Attribution of injury to alcohol (Longabaugh et al. , 1995) | x        |              |         |         |         |          |
| Severity of ER admission and diagnosis (medical records)           | x        |              |         |         |         |          |
| Quality of life (de Boer et al. , 2004)                     | x        |              | x       | x       | x       |          |
| Patient rating of the treatment (Lee et al. , 2007)         |          | x            |         |         |         |          |
| Working alliance inventory (Horvath and Greenberg, 1989)           |          | x            |         |         |         |          |
| Trait reactance (Shen and Dillard, 2005)                           |          |              | x       |         |         |          |

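### Protocol 11.4.3 names treatment as the only control for the mediator-outcome path, leaving the indirect effects open to confounding by baseline mediator level and possibly by baseline severity

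*Protocol*

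**What the plan says.** Section 11.4.3 specifies simple mediation (PROCESS Model 4) with two regressions. Path a is "the effect of the treatment condition on the hypothesized mediators"; path b is "the effect of each respective mediator on outcomes, while also controlling for the treatment effect on outcomes". Indirect effects are bootstrapped, and moderated mediation uses further PROCESS models. The section lists no covariates.

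Section 11.4.2, under the primary analysis and after the description of the GEE models, states: "Models will all be adjusted for the baseline AUDIT score". Section 11.4.3 neither repeats this sentence nor refers to it.

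Section 5.3 lists measures taken "in order to conduct moderation and mediation analysis". Read with 9.3.1 to 9.3.4, the schedule is:

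| Measure | Baseline value? |
|---|---|
| AUDIT (severity) | Yes |
| Readiness Rulers | Yes, then post-session |
| Actual-ideal discrepancy | Yes, then post-session and months 1, 3, 6 |
| Alcohol expectancies | Yes, then months 1, 3, 6 |
| Readiness to change questionnaire | No, first at month 1 |
| Self-efficacy scale | No, first at month 1 |
| Patient rating of treatment, working alliance | No, post-session only |
| Within-session behaviours (MI skills, change language) | None possible |

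The text on hypotheses in 11.4.3 names severity and readiness to change as moderating factors, not as covariates for path b.

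**The concern.** Participants are randomised to an intervention, not to a level of readiness, discrepancy or expectancies. Someone who arrives with high readiness may show both a higher later mediator and less later drinking, whatever the mediator itself does. A path b regression containing only treatment and the later mediator credits that shared origin to the mediator. Bootstrapping addresses the non-normal sampling distribution of the product of paths; it does nothing about confounding.

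Mechanisms are the trial's stated secondary objective (4.3). Aim 4 (3.1.5) uses the conclusions of the earlier aims to finalise and disseminate the intervention model, so a falsely identified mediator could shape the final product.

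**Working it through.** The protocol states no figure for the mediation analysis, so there is nothing of its own to reproduce. Every coefficient below is an assumption.

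**Sample size.** 11.2 gives 344 participants with 5-20% attrition: 344 × 0.95 ≈ 327 and 344 × 0.80 ≈ 275. N = 300 lies between these.

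**Step 1: closed form with one confounder.** Let ρ be the correlation between baseline and later mediator, c the correlation between baseline mediator and outcome, and a the treatment effect on the mediator in SD. Suppose the later mediator has no effect (true b = 0). With standardised variables, the treatment-only path b then estimates ρ × c, and the indirect effect is

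spurious indirect effect = a × ρ × c.

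**Step 2: numbers put in and compared with simulation.** These runs used N = 300, 200 to 500 simulated trials per scenario and 200 or 300 bootstrap resamples per trial. Where two values are shown, they come from separate runs.

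| a | ρ | c | a × ρ × c | Simulated indirect effect | Significant, treatment only | Significant, baseline mediator added |
|---|---|---|---|---|---|---|
| 0.30 | 0.6 | -0.40 | -0.072 | -0.071, -0.072 | 71.5%, 73% | 5.5%, 6% |
| 0.30 | 0.5 | -0.40 | -0.060 | -0.065, -0.059 | 75%, 65% | 7.5%, 8% |
| 0.30 | 0.4 | -0.30 | -0.036 | -0.037, -0.036 | 39%, 41% | 8.5%, 3% |
| 0.30 | 0.4 | -0.15 | -0.018 | -0.018 | 13% | 4% |
| 0.30 | 0.3 | -0.20 | -0.018 | -0.019 | 13% | not run |
| 0.30 | 0.2 | -0.20 | -0.012 | -0.012 | 7% | not run |
| 0.15 | 0.4 | -0.30 | -0.018 | -0.018 | 12% | not run |
| 0.15 | 0.3 | -0.20 | -0.009 | -0.009 | 4% | not run |

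The formula and the simulations agree. With 200 trials, the Monte Carlo standard error at a 5% rate is √(0.05 × 0.95 / 200) = 1.5 percentage points, so the adjusted rates are roughly nominal.

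**Step 3: two confounders, severity and baseline mediator.** This was a simulation of 1,000,000 participants with a = 0.25 and true b = 0. The coefficients are g (baseline mediator to later mediator), k (severity to later mediator), d (baseline mediator to outcome), h (severity to outcome) and r (correlation of severity with baseline mediator).

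| g, k, d, h, r | b, treatment only | b, plus severity | b, plus severity and baseline mediator |
|---|---|---|---|
| 0.5, 0.2, -0.2, 0.3, 0.3 | -0.005 | -0.101 | 0.002 |
| 0.5, 0.2, -0.1, 0.2, 0.3 | 0.016 | -0.049 | 0.002 |
| 0.6, 0.3, -0.1, 0.4, 0.3 | 0.125 | -0.068 | 0.003 |
| 0.3, 0.1, -0.1, 0.2, 0.2 | 0.002 | -0.027 | 0.002 |
| 0.5, 0, -0.2, 0.3, 0 | -0.097 | -0.098 | 0.002 |

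The treatment-only bias is negative, positive or close to zero, depending on whether the two confounders reinforce or cancel each other. Adjusting for severity alone leaves b between 0.03 and 0.10 too negative. Adjusting for both recovers the true value.

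With a true b of -0.20 (true indirect effect 0.25 × -0.20 = -0.05), the treatment-only b ranges from -0.297 to -0.075, an indirect effect of -0.074 to -0.019. Full adjustment gives about -0.198, an indirect effect of -0.049. A real mediator can therefore be understated as well as a null one invented.

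**The case against.** The strongest reply is that 11.4.3 does not say treatment is the sole regressor. The phrase defines path b in general terms, PROCESS Model 4 accepts covariates, and a covariate list for a secondary model may properly sit in a statistical analysis plan not seen here. A reader might infer that the protocol excludes baseline covariates; the text does not support that. What stands is narrower. The protocol chose to describe what path b controls for, named treatment, and gave no role to baseline values it collects in part for mediation analysis.

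Second, the AUDIT sentence in 11.4.2 says all models, and on a broad reading already covers severity. Its position under the primary analysis leaves its reach unclear, so severity is only conditionally part of this point. The broad reading does not settle the matter, because step 3 shows bias remaining after adjustment for severity alone.

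Third, a reader might infer that every needed baseline is already in hand. It is not. The self-efficacy scale and readiness questionnaire start at month 1, and within-session behaviours, treatment rating and working alliance have no baseline. The protocol does not treat the Readiness Rulers as equivalent to either scale.

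Fourth, the high false-positive rates come from the stronger assumed correlations; weaker ones give 4% to 13%. It would be wrong to infer that any mediator moved by treatment will be declared significant.

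**Conclusion.** The point holds as a weakness in a stated model. Followed as written, path b is open to confounding by baseline mediator level and, if the 11.4.2 sentence does not extend to 11.4.3, by baseline severity. That is different from showing that the eventual estimates will be confounded.

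The qualitative conclusion rests only on the mediator not being randomised. The size rests entirely on assumed correlations, for which the document offers no anchor. The ranges in the working illustrate what is possible; they do not predict this trial, and the direction of bias cannot be known in advance.

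The consequence is confined to the mechanism analyses of Aim 3 and what Aim 4 draws from them. The comparison of the randomised groups on the primary outcomes is unaffected.

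**What to change.** In 11.4.3:

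- State that baseline AUDIT enters both the path a and path b equations and the moderated-mediation models. This also settles the reach of the 11.4.2 sentence.
- Add the baseline value of the same mediator to those equations where it is measured: Readiness Rulers, actual-ideal discrepancy and alcohol expectancies.
- For mediators without a baseline (self-efficacy scale, readiness to change questionnaire, within-session behaviours, treatment rating, working alliance), adjust for AUDIT and, as a proxy at most, the baseline Readiness Rulers. Report these indirect effects as exploratory, with a sensitivity analysis for unmeasured confounding.

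Fix the covariates before outcome data are examined, since 6.2.2 says analysts will not be blinded.

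The cost is analysis wording and one added sensitivity analysis; no new data are needed. Section 2.3 gives the form of statistical analysis as an example of a significant change, so a protocol edit may need ethics committee approval. The missing baselines cannot be recovered by wording, which is why those mediators need the exploratory label.
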